### Statistical analysis

The analysis of the primary endpoint that BARC type 2–5 bleeding events require medical intervention for 6 months based on intention-to-treat (ITT) and per-protocol (PP) population. The ITT population is all randomized subjects. All randomized subjects without major protocol violations, subjects who did not receive the assigned treatment, or did not receive any treatment belong to the ITT population. The PP population is fully in line with the study. The study will conduct subgroup analyses of primary and secondary endpoints based on gender, age, and diabetes in the ITT population. Multiple imputation will be performed to handle missing data. The main endpoints of the ITT population are analyzed and then reanalyzed in the PP population to support the results. The analysis of the composite of MACCE is based on the ITT population. Unless otherwise stated, all hypothesis tests are carried out at a bilateral significance level of 5%. To determine whether the efficacy and safety of rivaroxaban plus clopidogrel in patients with CHD and GID are not inferior to aspirin plus clopidogrel. The difference in the incidence of endpoints between the experiment group and the control group is less than or equal to the non-inferior effect value means an invalid hypothesis (H0, P0–P1 ≤  − 4.7%). The difference in the incidence of the primary endpoint between the two groups is greater than the non-inferior effect value remains an alternative hypothesis (H1, P0–P1 >  − 4.7%). The non-inferiority test is carried out at a significance level of 0.025 on one side. Statistical analyses were performed with SAS version 9.3.

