**Discussion:**

The objective of this study is to evaluate the efficacy and safety of rivaroxaban plus clopidogrel versus aspirin plus clopidogrel in patients with CHD and GID undergoing PCI. We aim to explore an optimized antithrombotic strategy, which achieves the same anti-ischemic effect as standard DAPT without increasing the risk of GIB, for patients with CHD and GID undergoing PCI.

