### Endpoints

The primary endpoint of the study is Bleeding Academic Research Consortium (BARC) type 2–5 bleeding events requiring medical intervention. The secondary endpoint is a composite of MACCE including all-cause death, cardiac death, nonfatal myocardial infarction, stent thrombosis, ischemia-driven target vessel revascularization, and stroke. Other endpoints include the separate components of the MACCE and BARC 3–5 bleeding. Detailed definitions of all study endpoints are provided in Supplemental file 3.

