## Discussion

Platelet activation and aggregation play an important role in atherosclerotic thrombosis. Therefore, antiplatelet is crucial to treat CHD and reduce the occurrence of ischemic events after PCI [13]. The study aims to investigate the safety and efficacy of rivaroxaban plus clopidogrel in Chinese CHD and GID patients undergoing PCI, and whether the same anti-ischemic effect as standard DAPT therapy is obtained without increasing the risk of GIB in patients with gastrointestinal injury. Conventional platelet oxidase inhibitors, such as aspirin, can damage the gastrointestinal mucosa and are 4–6 times more likely to cause gastrointestinal injury due to anti-platelet activation. While P2Y_12_ receptor antagonists, such as clopidogrel, also have an increased risk of GIB, but by a different mechanism from aspirin, increasing the risk of gastrointestinal injury secondary to impaired platelet-derived growth factor release. These growth factors promote endothelial cell proliferation and accelerate mucosal healing. Clopidogrel can make gastrointestinal injury more severe in combination with aspirin [14]. Previous studies have demonstrated the safety and efficacy of NOAC in combination with an antiplatelet agent in patients with CHD and atrial fibrillation (AF), but no studies have further analyzed the safety and efficacy of NOAC plus clopidogrel in CHD and GID. No increase or even reduces the risk of gastrointestinal bleeding in patients with GID and obtains the same anti-ischemic effect as conventional DAPT (Table 3). The anti-ischemic effect of DAPT, especially within 30 days, was investigated.

**Table 3 Tab3:** Recent clinical studies on antithrombotic regimens in patients receiving long-term OAC therapy

Study title (year)	Patient population	Method	Conclusion
**WOEST (2013) **[9]	573 patients treated with OAC and undergoing PCI	① OAC combined with clopidogrel; ② OAC combined with clopidogrel and aspirin. Antiplatelet therapy in SCAD patients (1 month–1 year); at least 1 year of clopidogrel treatment in ACS patients	Dual antithrombotic reduces bleeding complications (19.4% VS. 44.4%, HR = 0.36, 95% CI 0.26 ~ 0.50, *P* < 0.0001), does not increase the incidence of thrombotic events

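### Efficacy is placed under the non-inferiority claim, but the only margin and the sample size belong to bleeding, so the plan has no test that could support the MACCE half of its conclusion

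*Protocol article*

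**What the plan says.** The aim has two halves. The Discussion paragraph of the abstract seeks a strategy "which achieves the same anti-ischemic effect as standard DAPT without increasing the risk of GIB", and the main Discussion asks "whether the same anti-ischemic effect as standard DAPT therapy is obtained without increasing the risk of GIB". The Statistical analysis section puts both halves under non-inferiority: "To determine whether the efficacy and safety of rivaroxaban plus clopidogrel in patients with CHD and GID are not inferior to aspirin plus clopidogrel".

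The endpoints divide the same way. Under Endpoints, "The primary endpoint of the study is Bleeding Academic Research Consortium (BARC) type 2–5 bleeding events requiring medical intervention", and "The secondary endpoint is a composite of MACCE including all-cause death, cardiac death, nonfatal myocardial infarction", followed by stent thrombosis, ischaemia-driven target vessel revascularisation and stroke.

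The Sample size section takes a 6% rate of BARC type 2–5 bleeding in each arm at 6 months, a margin of 4.7%, a one-sided type 1 error of 2.5%, 85% power and 10% drop-out, and arrives at 1020 patients. The article gives no MACCE rate, margin or power.

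For analysis, the Statistical analysis section says "The analysis of the composite of MACCE is based on the ITT population". It also sets a default: unless otherwise stated, "all hypothesis tests are carried out at a bilateral significance level of 5" per cent. H0 is worded for the incidence of endpoints, in the plural and unspecified. H1 is worded for the incidence of the primary endpoint. Both use the same limit of −4.7% for P0–P1.

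**The concern.** The stated claim and the stated test rules do not fit each other. Non-inferiority of efficacy is announced, but the text leaves only two ways to reach it:

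- **The wording of H0 governs.** The 4.7-point margin then also covers MACCE. It was set for bleeding, and nothing in the article justifies it for ischaemic events.
- **The wording of H1 governs.** MACCE then falls to the default two-sided 5% difference test. Failing to find a difference does not establish non-inferiority or sameness, least of all in a trial that was not sized for the endpoint.

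Loss of ischaemic protection when aspirin is left out after PCI is half of the trial's own question. As the section stands, the trial could meet its bleeding criterion and also state an efficacy conclusion while a substantial rise in MACCE had not been ruled out.

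**Working it through.** **1. What the sample size belongs to.** Inputs from the Sample size section: p = 0.06 in both arms, margin 0.047, one-sided 2.5% (z = 1.960), power 85% (z = 1.036), drop-out 10%. With unpooled variance:

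n per arm = (1.960 + 1.036)² × 2 × 0.06 × 0.94 / 0.047² = 458.5, so 459; total 918; 918 / 0.90 = 1020.

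The stated figure reproduces exactly from the bleeding inputs alone. Nothing in it is sized for MACCE.

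**2. Assumptions for MACCE.** The article gives no MACCE rate, so control rates of 2%, 4% and 6% at 6 months are assumed. Two sample sizes are used: 459 per arm (after the planned drop-out) and 510 per arm (all randomised, as ITT is defined, ignoring information lost through drop-out).

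**3. The default two-sided 5% test.** For a true 1.5-fold excess, p₁ = 1.5 p₀:

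power = Φ[(p₁ − p₀)/SE − 1.96], with SE = √{[p₀(1 − p₀) + p₁(1 − p₁)]/n}.

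Example, 4% against 6% with n = 459: SE = √[(0.0384 + 0.0564)/459] = 0.01437; 0.02/0.01437 = 1.392; Φ(1.392 − 1.960) = 0.28.

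| Control rate | True rate, test arm | Power, 459 per arm | Power, 510 per arm |
|---|---|---|---|
| 2% | 3% | 16% | 17% |
| 4% | 6% | 28% | 31% |
| 6% | 9% | 41% | 45% |

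At each of these rates, with either sample size, a non-significant result is more likely than not even though MACCE is truly 50% higher. With 459 per arm its probability is about 84%, 72% and 59%.

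**4. What identical observed rates would leave open.** Suppose 4% is observed in both arms of 459.

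- Risk difference: 1.96 × √(2 × 0.04 × 0.96/459) = 0.0254, a 95% confidence interval of about ±2.5 points.
- Relative risk, log scale: expected events 0.04 × 459 = 18.36 per arm; SE = √[2 × (1/18.36 − 1/459)] = 0.323; upper limit exp(1.96 × 0.323) = 1.9.

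Dividing the risk-difference limit by the control rate, (4 + 2.54)/4 = 1.6, is not a substitute, because it treats the control rate as known.

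**5. Reusing 4.7 points for MACCE.** Relative risk tolerated = (p₀ + 4.7)/p₀, in percentage points:

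- 2%: 6.7/2 = 3.35
- 4%: 8.7/4 = 2.2
- 6%: 10.7/6 = 1.8

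**The case against.** **MACCE is secondary and the analysis plan is not shown.** A margin, power or testing order for a secondary endpoint is commonly left to the analysis plan, and a secondary endpoint need not be powered. This stands: the absence of a MACCE margin is not itself the fault. What remains is on the page, namely an efficacy non-inferiority claim, one bleeding margin, and an H0 and H1 of different scope.

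**The plural in H0 may be loose English.** That is plausible, since both formulas use the same quantity and limit, and H1 names only the primary endpoint. But if the bleeding-only reading is right, the sentence claiming non-inferior efficacy has no test behind it.

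**A reader might infer that a non-significant MACCE test will be reported as equivalence.** No sentence says so. The abstract speaks of exploring a strategy and the Discussion asks whether the effect is obtained; neither is a decision rule. The inference comes from combining the aim with the default test, and should be presented only as an inference.

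**A reader might also infer that MACCE is analysed in ITT alone.** The text does not settle this. The sentence just before the MACCE one has the main endpoints, in the plural, repeated in the PP population as support, and that could include MACCE. The section is ambiguous here, not plainly restrictive.

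**The MACCE rates are assumed.** This is true, and higher rates ease the problem. Within 2% to 6% the conclusion does not change, and moving from 459 to 510 per arm raises power by only 1 to 4 points.

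**Conclusion.** The point holds as a conflict between a stated claim and stated rules. The plan claims non-inferiority for efficacy as well as safety, but its margin and sample size are for bleeding, and neither available reading of the MACCE analysis can carry the efficacy half. On the assumed control rates of 2% to 6%, the default test would usually miss a true 1.5-fold excess, and the borrowed margin would accept relative risks from about 1.8 up to about 3.4. These sizes depend on assumed rates, on normal approximations and on 459 or 510 patients per arm. The inconsistency itself depends on none of them.

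The primary bleeding analysis is unaffected by this point, and its sample size reproduces. The documents do not show that the investigators have committed to treating non-significance as sameness, and the point does not rely on that.

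**What to change.** In the Statistical analysis section:

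1. Word both H0 and H1 for the primary bleeding endpoint, and limit the 4.7-point margin and the non-inferiority claim to it.
2. Report MACCE as a risk difference and a relative risk, each with a 95% confidence interval, in the ITT population. State explicitly that the PP analysis of MACCE is supportive, which removes the present ambiguity.
3. Reword the aim and the planned conclusion, in the abstract and the Discussion as well, along the lines of: *bleeding non-inferiority; ischaemic effect estimated, not established*.

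The cost is an amendment with ethics approval and a registry update, the route already described under Protocol amendments, plus a more modest efficacy claim. No more patients are needed.

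A new MACCE margin is not required. Trial status reports 720 patients recruited and 506 with complete 6-month follow-up, and the trial is open-label, so a margin chosen now could be challenged as set after data had accrued. At this sample size it would probably also be underpowered: with equal true rates of 4% and 459 per arm, a margin equal to a 1.5-fold rate (illustrative only) would have about 34% power.

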### Clinical Events Committee and Data and Safety Monitoring Board

The Clinical Events Committee (CEC) is composed of medical experts in the field of cardiology and gastroenterology. Committee members are responsible for reviewing all reported events and classifying those events. If necessary, CEC can request original information from the research center. Members are remaining blind to treatment assignments.

The study is monitored by an independent Data and Safety Monitoring Board (DSMB). All adverse events in this study will be reported to the DSMB, and they can request additional information as required. The DSMB will regularly check the endpoint events to identify the safety of the study. DSMB will supervise and manage the research scheme and data before the start of the study, mid-study, and after the end of the study. Based on the result of the review, the DSMB will provide a report about the safety of the study to the lead investigator. And based on safety data, the DSMB may recommend that the lead investigator modify or terminate the trial.

### Protocol amendments

During the course of the trial, any formal modifications to the protocol or informed consent form will be agreed by the research team, approved by the Ethics Committee to implementation, and reported to participants if necessary. It will also be updated in the Clinical Trials Registry.

## Discussion

Platelet activation and aggregation play an important role in atherosclerotic thrombosis. Therefore, antiplatelet is crucial to treat CHD and reduce the occurrence of ischemic events after PCI [13]. The study aims to investigate the safety and efficacy of rivaroxaban plus clopidogrel in Chinese CHD and GID patients undergoing PCI, and whether the same anti-ischemic effect as standard DAPT therapy is obtained without increasing the risk of GIB in patients with gastrointestinal injury. Conventional platelet oxidase inhibitors, such as aspirin, can damage the gastrointestinal mucosa and are 4–6 times more likely to cause gastrointestinal injury due to anti-platelet activation. While P2Y_12_ receptor antagonists, such as clopidogrel, also have an increased risk of GIB, but by a different mechanism from aspirin, increasing the risk of gastrointestinal injury secondary to impaired platelet-derived growth factor release. These growth factors promote endothelial cell proliferation and accelerate mucosal healing. Clopidogrel can make gastrointestinal injury more severe in combination with aspirin [14]. Previous studies have demonstrated the safety and efficacy of NOAC in combination with an antiplatelet agent in patients with CHD and atrial fibrillation (AF), but no studies have further analyzed the safety and efficacy of NOAC plus clopidogrel in CHD and GID. No increase or even reduces the risk of gastrointestinal bleeding in patients with GID and obtains the same anti-ischemic effect as conventional DAPT (Table 3). The anti-ischemic effect of DAPT, especially within 30 days, was investigated.

**Table 3 Tab3:** Recent clinical studies on antithrombotic regimens in patients receiving long-term OAC therapy

Study title (year)	Patient population	Method	Conclusion
**WOEST (2013) **[9]	573 patients treated with OAC and undergoing PCI	① OAC combined with clopidogrel; ② OAC combined with clopidogrel and aspirin. Antiplatelet therapy in SCAD patients (1 month–1 year); at least 1 year of clopidogrel treatment in ACS patients	Dual antithrombotic reduces bleeding complications (19.4% VS. 44.4%, HR = 0.36, 95% CI 0.26 ~ 0.50, *P* < 0.0001), does not increase the incidence of thrombotic events
**PIONEER AF-PCI (2016) **[10]	2124 patients with PCI in combination with AF	① Rivaroxaban (15 mg qd) in combination with clopidogrel for 12 months; ② rivaroxaban (2.5 mg bid) in combination with DAPT for 1, 6, or, 12 months; ③ VKA combined with DAPT treatment for 1, 6, or 12 months	The incidence of clinically significant bleeding was lower in both rivaroxaban groups than in the standard triple antithrombotic group (16.8% vs. 18.0% vs. 26.7%; HR 0.59 and 0.63, respectively); central mortality was similar in the 3 groups
**RE-DUAL PCI (2017) **[15]	2725 patients with non-valvular AF who underwent PCI	① Dabigatran (100 mg bid) in combination with P2Y_12_ receptor inhibitor; ② dabigatran (150 mg bid) in combination with P2Y_12_ receptor inhibitor; ③ warfarin combined with DAPT	Dual antithrombotic is not inferior to triple antithrombotic in reducing the risk of ischemia, and the risk of bleeding is lower than in the triple antithrombotic group (15.4%VS. 26.9%, HR = 0.52, 95% CI 0.42 ~ 0.63, *P* < 0.0001)
**ENTRUST-AF PCI (2019) **[16]	1506 patients with AF who underwent PCI	① Edoxaban (60 mg qd) in combination with P2Y_12_ receptor inhibitor; ② VKA United DAPT. Aspirin therapy for 1 to 12 months (physician weighs), remaining medications for 12 months	Dual antithrombotic is non-inferior to triple antithrombotic in terms of bleeding (17% VS. 20%, *HR* = 0.83, 95% *CI* 0.65 ~ 1.05, non-inferior *P* = 0.001), no statistically significant difference in terms of ischemic events
**AUGUSTUS (2019) **[17]	4614 patients with AF with a recent history of ACS or PCI and treated with a P2Y_12_ receptor inhibitor (clopidogrel was chosen in 92.6% of patients)	Apixaban (5 mg or 2 mg bid depending on the patient) or VKA combined with aspirin or placebo (2 × 2 analysis design, 4 groups) for 6 months	P2Y_12_ receptor inhibitor-based apixaban is superior to dual antithrombotic with VKA and triple antithrombotic with aspirin
**Gemini-ACS-1 (2017) **[11]	3027 patients with ACS	① Received low-dose rivaroxaban (2.5 mg qb) plus a P2Y_12_ inhibitor (clopidogrel or tigretol); ② Aspirin (100 mg bid) plus P2Y_12_ inhibitor(clopidogrel or tigretol)	A dual pathway antithrombotic therapy approach combining low-dose rivaroxaban with a P2Y_12_ inhibitor for the treatment of patients with acute coronary syndromes had a similar risk of clinically significant bleeding as aspirin and a P2Y_12_ inhibitor

*OAC* oral anticoagulant, *PCI* percutaneous coronary intervention, *AF* atrial fibrillation, *ACS* acute coronary syndrome, *SCAD* stable coronary artery disease, *qd* once daily, *bid* twice daily, *DAPT* dual antiplatelet therapy, *VKA* vitamin K antagonist, *DES* drug-eluting stent

Bleeding events after PCI are independently associated with increased mortality, bleeding has become an important prognostic indicator for patients with ACS, and reducing bleeding events has become a major goal to improve the outcome of antiplatelet therapy. Bleeding events reduce patient compliance with medication and further increase prognostic risk. Although studies have confirmed the protective effect of PPI on the drug-induced injury of the gastrointestinal tract (such as aspirin and clopidogrel) [5], clopidogrel combined with PPI significantly reduces gastrointestinal adverse effects and has no significant differences in cardiovascular events. But pharmacokinetics studies have shown that some PPIs even can affect the antiplatelet reactivity of clopidogrel. Not all patients get the benefit from concomitant antiacid therapy [18]. Furthermore, PPI application does not fundamentally reduce the risk of bleeding associated with DAPT. It is noteworthy that anticoagulants do not cause gastrointestinal damage.

The 2020 ESC guidelines for atrial fibrillation recommend discontinuing aspirin within 1-week and continuing (N)OAC in combination with a P2Y_12_ receptor inhibitor for up to 12 months in patients with atrial fibrillation and ACS parallel uncomplicated PCI if the risk of stent thrombosis is low or the risk of bleeding is higher than the risk of ischemia [19]. Previous studies in patients with atrial fibrillation combined with CHD, including WOEST [9], PIONEER AF-PCI [10], RE-DUAL PCI [15], ENTRUST-AF PCI [16], AUGUSTUS [17], and GEMINI-ACS-1 [11], have demonstrated that OAC in combination with an antiplatelet agent is more effective than conventional DAPT or triple OAC + DAPT. But these studies were heterogeneous with the Asian yellow population, and most of the studies enrolled Caucasians [9–11, 15–17]. Rivaroxaban is the first oral, direct Factor Xa inhibitor to receive approval from regulatory authorities for stroke prevention in patients with AF, based mainly on the Phase III results of the ROCKET AF trial [20]. Rivaroxaban has certain advantages over warfarin and other VKAs in efficacy and safety in diseases at high risk of thrombosis, including ACS. Since factor Xa plays a central role in thrombosis, inhibition of factor Xa with low-dose rivaroxaban might improve cardiovascular outcomes in patients with recent ACS. It has the advantages of rapid onset of action, predictable efficacy, no need for routine coagulation monitoring, and conventional-dose adjustment [21, 22].

Dual antithrombotic therapy with rivaroxaban 15 mg once daily plus clopidogrel is a feasible treatment strategy among patients undergoing PCI with AF in the PIONEER AF-PCI trial [10]. The study of Lin et al. [23] demonstrated that low-dose rivaroxaban 10 mg once daily was associated with equal risks of ischemic stroke, systemic embolism, or major and nonmajor clinically relevant bleeding compared with the standard dose rivaroxaban 15 mg or 20 mg once daily in Asian patients with AF. There are a lower risk of ischemia and a higher risk of bleeding in Asian populations. In this study, patients undergoing PCI without AF are receiving clopidogrel and rivaroxaban 10 mg once daily in terms of efficacy and safety.

If the results of this study are reasonable, it will provide a new strategy for the secondary prevention of CHD combined with GID undergoing PCI and more evidence for guidelines.

## Conclusion

This study is the first trial to investigate the safety and efficacy of rivaroxaban plus clopidogrel as an alternative to DAPT after PCI in patients with CHD and GID.

## Trial status

This study is under participant recruitment. The first patient was included on 8th Apr. 2021, and the recruitment will be finished on 31st Dec. 2023. At present, 720 patients have been recruited, and 506 of them with complete follow-up visits of 6 months.

### Dissemination policy

The results of the study will be disseminated to participants, the public, and other relevant groups through publications and presented at scientific conferences.

## Abbreviations

DAPT: Dual antiplatelet therapy
CHD: Coronary atherosclerotic heart disease
PCI: Percutaneous coronary intervention
GID: Gastrointestinal diseases
BARC: Bleeding Academic Research Consortium
MACCE: Major adverse cardiovascular and cerebrovascular events
UGIB: Upper gastrointestinal bleeding
ACS: Acute coronary syndrome
NSTE-ACS: Non-ST segment elevation acute coronary syndromes
GRACE: Global Registry of Acute Coronary Events
NSTEMI: Non-ST segment elevation myocardial infarction
STEMI: ST-segment elevation myocardial infarction
PPI: Proton pump inhibitors
ITT: Intention-to-treat
PP: Per-protocol
CEC: Clinical Events Committee
DSMB: Data and Safety Monitoring Boards
VKA: Vitamin K antagonist
OAC: Oral anticoagulant
NOAC: New oral anticoagulant
AF: Atrial fibrillation
